### Outcomes

#### Primary clinical outcome

The between-group difference in the number of headache days in the first 28 days after the infusion is the primary outcome of this trial. A headache day is defined as a day in which the headache lasts 4 or more hours or a headache of any duration for which abortive treatment (anti-inflammatories, triptans, ergot derivatives, opioids) is taken. During the trial, participants will be asked to keep track of their headache days in a diary.

#### Secondary outcomes

Number of headache days in periods from 29 to 56 days and 57 to 84 days after the infusion; the between-group difference in the number of headache days from 29 to 56 days and 57 to 84 days after the infusion.

The following will be assessed at baseline and from 1 to 28 days, 29 to 56 days, and 57 to 84 days after the infusion:Pain intensity: average intensity of headaches as measured on an 11-point Numerical Rating Scale (NRS; 0–10) [20]. During the trial, participants will be asked to rate their daily average pain level in a diary. The baseline headache intensity will be calculated as the mean of the daily pain score in the 28 days before the trial infusion.Duration of headache episodes: the duration of the (daily) headache will be measured in hours in the pain diary. The baseline headache duration will be calculated as the mean of the duration of daily headaches in the 28 days before the trial infusion.Time until the new onset of headache: determine the average number of days until the recurrence of headache after the trial infusion.Sleep duration and quality: average daily duration of sleep as measured by the actigraphy wearable device (for 28 days after the infusion).Sleep quality: quality of sleep as measured by the Pittsburgh Sleep Quality Index (PSQI) [21].Physical activity: average daily physical activity as measured by the actigraphy wearable device (at 28 days after the infusion) and Brief Pain Inventory (BPI) [22].Functioning: impact of headaches on functioning as measured by the Headache Impact Test (HIT-6) [23] score and Migraine Disability Assessment (MIDAS) [24].Psychological health: emotional function as measured by Generalized Anxiety Disorder-7 items (GAD-7) [25], Pain Catastrophizing Scale (PCS) [26], and Patient Health Questionnaire for Depression-9 items (PHQ-9) [27] instruments.Quality of life: health-related quality of life measured by EuroQol-5 dimensions, 5-item questionnaire (EQ-5D-5L) [28].Participant satisfaction: participant satisfaction as measured by the Participant Global Impression of Change (PGIC) [29].Adverse effects: adverse effects of ketamine as measured on the Clinician-Administered Dissociative States Scale (CADSS) [30] and Bowdle [31] questionnaires at end of the infusion.Analgesic consumption: analgesic consumption will be measured by intake frequency and doses of headache-specific (abortive and prophylactic) medication and average daily oral morphine equivalent (OME) in milligrams.

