## Introduction

### Background and rationale

The prevalence of primary chronic daily headaches (CDH) is 5% in the population and is associated with significant morbidity, a poor quality of life, and a substantial burden on the healthcare system [1]. Important subtypes of CDH include chronic migraine, chronic tension-type headache, hemicrania continua, new daily persistent headache, and medication overuse headache [2–5]. Many patients with CDH do not respond to conventional medical management that includes medications, nerve blocks, and psychological approaches, and adverse events with these treatments are also common [6, 7]. Although onabotulinum-toxin A and calcitonin gene-related peptide (CGRP) antagonists are promising new treatments for CDH, these are expensive and their long-term effects are unclear. There is an urgent need for efficacious, safe, inexpensive, and widely available treatments for patients with CDH.

The subtypes of CDH share central sensitization, an increase in neuronal excitability secondary to repetitive stimulation of the nociceptive C-fibers (“wind-up”) in the trigeminocervical complex (TCC) and the brain, as a common mechanism [8–10]. The TCC contains major relay neurons for nociceptive afferent input from the meninges and cervical structures and its sensitization is a key feature of CDH. Central sensitization is mediated primarily by *N*-methyl-d-aspartate (NMDA) receptors. Activation of the NMDA receptors also plays a major role in ongoing pain, opioid-induced hyperalgesia, and mood dysregulation [10]. This sensitization can be reversed on a long-term basis by the blockade of NMDA receptors by non-competitive antagonists such as ketamine [8–10]. Intravenous (IV) ketamine in high doses (0.4 to 1 mg. kg^−1^ .h^−1^) has been used to treat NMDA receptor-driven neuropathic pain syndromes [8].

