### Eligibility criteria

The inclusion and exclusion criteria are listed in Table 1. After enrollment, bloodwork to rule out hepatic and/or renal impairment is ordered if no recent (within 12 months) information is available. Additionally, on the day of the intervention, a pregnancy test is performed for each female participant less than 50 years of age.

**Table 1 Tab1:** Inclusion and exclusion criteria

***Inclusion criteria*****:** 1. Age 18 years or older 2. CDH diagnosis according to the International Classification of Headache Disorder – 3rd edition [18] 3. Normal liver and kidney function ***Exclusion criteria*****:** 1. Pregnant or breastfeeding participants 2. Pre-existing renal impairment: stage 4 chronic kidney disease 3. Pre-existing liver impairment, defined as alanine transaminase (ALT) and/or aspartate aminotransferase (AST) greater than two times the upper normal limit, an elevated total bilirubin (TB), an elevated alkaline phosphatase (AP), an elevated international normalized ratio (INR) for prothrombin time, and/or an elevated blood urea nitrogen (BUN) 4. Chronic benzodiazepine or antipsychotic medication use 5. History of a cerebrovascular event 6. Significant and untreated hypertension and severe cardiac decompensation 7. Pheochromocytoma 8. Hyperthyroidism 9. Glaucoma 10. Concomitant use of strong CYP2B6 or CYP2C8 inhibitor 11. Allergy or intolerance to ketamine 12. Any significant cognitive or language barriers that impede participation 13. Use of calcitonin gene-related peptide antagonists in one month or onabotulinum-toxin A in 3 months prior to the trial medication infusion, that is associated with greater than 30% reduction in headache intensity or number of migraine days 14. Active diagnosis of post-traumatic stress disorder 15. Active diagnosis of substance use disorder 16. Daily oral morphine equivalent (OME) of 80 mg or higher	

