### Statistical methods

The normality of the trial data will be assessed, means and standard deviation (or median and interquartile ranges, as appropriate) will be used to summarize continuous data, and frequencies and proportions will be used for categorical data. To compare data between the 2 groups, categorical outcomes will be analyzed with the chi-square test and continuous variables will be analyzed with independent *t*-tests (or Wilcoxon rank sum test). A baseline-adjusted ANCOVA model will be employed for all outcome variables of interest for which a baseline is recorded in the 28 days interval prior to treatment. In addition, for the primary outcome, an additional ANCOVA model will be employed adjusting for baseline headache days and the following variables that are strongly associated with this outcome: number of headache years, depression/anxiety, intensity of headache, and opioid intake. Estimates of differences in means (with 95% CI) at 28, 56, and 84 days will be provided for continuous outcomes. A Cox proportional hazards model will be built to investigate the effect on variables on the time to a specified event. Missing primary outcome data will not be imputed. A sensitivity analysis assuming the participants lost to follow-up showed no improvement (i.e., they had no change in headache frequency) will then be performed. Group comparisons will be performed in responders (defined as a reduction in pain by 3 or more headache days in 28 days from baseline at 28 days after the infusions) versus non-responders, participants on Botox/CGRP antagonist treatment versus none, comparison across different subtype of CDH, and baseline frequency and average intensity of headaches. An intention-to-treat analysis approach will be used. SAS Studio Edition will be used to conduct the analyses.

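### Time to headache recurrence is summarised as an average number of days and the Cox model names no event, so participants without a recurrence, or whose headache never stops, have no defined place in the comparison

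*Protocol article*

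**What the plan says.** Objectives lists the number of days until headache returns as a secondary objective. Secondary outcomes labels the item as time until a new onset and gives its measure: "determine the average number of days until the recurrence of headache after the trial infusion". The sentence that introduces this list of outcomes reads "The following will be assessed at baseline and from 1 to 28 days, 29 to 56 days, and 57 to 84 days after the infusion".

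Statistical methods gives two routes that could apply. The general rule is that "continuous variables will be analyzed with independent *t*-tests (or Wilcoxon rank sum test"). Separately, "A Cox proportional hazards model will be built to investigate the effect on variables on the time to a specified event". The article does not say which event is meant or tie the model to this outcome. The stated rule for missing data concerns the primary outcome only.

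Background and rationale counts these among the subtypes of chronic daily headache (CDH): "chronic migraine, chronic tension-type headache, hemicrania continua, new daily persistent headache, and medication overuse headache". Table 1 requires a "CDH diagnosis according to the International Classification of Headache Disorder – 3rd edition" and excludes no subtype. The only event-like definition in the article belongs to the primary outcome: "A headache day is defined as a day in which the headache lasts 4 or more hours or a headache of any duration", the second part applying when abortive treatment is taken. It is not linked to recurrence.

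**The concern.** Two kinds of participant do not fit the stated measure.

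- **No recurrence observed.** The diary runs for 84 days. A participant who is still headache-free then, or who is lost earlier, has no number of days to average.
- **Headache that never stops.** Taken literally, a headache must stop before it can recur or have a new onset. Two of the admitted subtypes are by name continuous or daily persistent. The article does not say whether an uninterrupted headache counts as an immediate event, as no event, or as not evaluable.

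If both kinds are left out, what remains is a subset selected by what happened after randomisation, which does not sit well with the intention-to-treat approach in Statistical methods. If participants whose headache never stops are instead censored at day 84 as not having recurred, the worst outcomes are scored as the best. At stake is the answer to one listed secondary objective.

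The baseline listing is a smaller error of the same kind. Statistical methods applies a baseline-adjusted ANCOVA to outcomes with a recorded baseline, and this outcome cannot have one.

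**Working it through.** **The plan's own figures.** None is given for this outcome. The sample size statement (difference 3, SD 3.8, two-sided 0.05) gives 26 per arm by the normal approximation against the stated 25, with power at 25 of 79.7% (normal) or 78.1% (t), and 25/(1 − 0.10) = 27.8, so 28 enrolled. That is close to what is stated, and nothing below depends on it.

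**Inputs.** From the article: 84 days of follow-up and 25 evaluable participants per arm. Assumed, because the article gives nothing: the proportions whose headache never stops or who stay free to day 84, and the mean days to recurrence.

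**Worked example (assumed counts, 25 per arm).** Placebo: 15 never stop, 10 recur on day 6. Ketamine: 5 never stop, 15 recur on day 4, 5 stay free to day 84.

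- Mean among recurrers only: ketamine 4, placebo 6. This favours placebo.
- Mean over all, with 0 for never stopped and 84 for free throughout: ketamine (5×0 + 15×4 + 5×84)/25 = 480/25 = 19.2; placebo (15×0 + 10×6)/25 = 2.4. This favours ketamine.
- Event-free at day 84 if never-stopped is censored: ketamine (5 + 5)/25 = 40%, placebo 15/25 = 60%. If never-stopped is an event at the start: ketamine 5/25 = 20%, placebo 0%.

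**A milder set of assumptions.** Placebo: 60% never free, 40% recur at mean 3 days. Ketamine: 30% never free, 60% recur at mean 7 days, 10% free to day 84. Among recurrers the difference is 7 − 3 = 4 days. Over all it is (0.6×7 + 0.1×84) − 0.4×3 = 12.6 − 1.2 = 11.4 days, of which 0.1×84 = 8.4 comes from the last assumption. Here the recurrers-only mean keeps its sign and understates the difference. In 300 simulated trials with 28 per arm, the Cox hazard ratio (HR, ketamine/placebo) was 1.55 with never-free participants censored and 0.42 with them counted as events at the start.

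**Range of assumptions.** Simulation, 25 per arm, exponential times to recurrence. P/K = placebo/ketamine; differences are ketamine minus placebo, in days.

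| Never stop P/K | Free to day 84 P/K | Mean recurrence P/K | Difference, recurrers only (trials with wrong sign) | Difference, all participants (0 and 84 assigned) | Median HR, never-stopped censored | Median HR, never-stopped = event at start |
|---|---|---|---|---|---|---|
| 50/20% | 0/20% | 7/5 | −2.0 (79%) | 16.3 | 1.40 | 0.52 |
| 50/20% | 0/10% | 7/7 | 0.0 (49%) | 9.9 | 1.66 | 0.56 |
| 50/20% | 0/10% | 7/10 | 3.0 (16%) | 12.1 | 1.52 | 0.48 |
| 30/20% | 0/10% | 7/7 | 0.1 (44%) | 8.4 by hand | 1.00 | 0.67 |
| 0/0% | 0/20% | 7/5 | −1.8 (87%) | 13.8 by hand | 0.68 | 0.68 |

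Means in the first three rows use 5,000 trials. Means in the last two rows, and all hazard ratios, use 300 (standard error of a percentage up to about 3 points). By hand, row 4 is (0.7×7 + 0.1×84) − 0.7×7 = 8.4 and row 5 is (0.8×5 + 0.2×84) − 7 = 13.8.

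Two things follow. With headaches that never stop, their coding alone can move the hazard ratio from one side of 1 to the other; without them, the Cox result does not depend on the rule. The recurrers-only mean can mislead either way, because it also drops those who stay headache-free.

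**The case against.** The item's label suggests a plain reading: time from infusion to the next headache. On that reading a continuing headache is an event on day 1, and the difficulty with persistent headache disappears. This is also the only time-to-event outcome in the list, so the Cox model is most naturally meant for it, and a Cox model would censor participants who are headache-free at day 84 or lost. Reporting an average beside a Cox model is not a contradiction. Event definitions and censoring rules commonly sit in the full protocol or analysis plan, which are not shown.

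Most of this stands. A reader might infer that the plan excludes participants whose headache never stops, or censors them as successes. No section says so. A reader might also infer that many participants will never be headache-free; the article admits such subtypes but does not give their share. Censoring detail that may be written elsewhere is not counted as a fault here.

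What the objection does not remove is what the article itself states: an average as the measure of a time that will be unobserved for some participants, a baseline assessment that cannot exist, and a Cox model whose event has to be guessed. The plain reading is sensible, but recurrence and new onset both point away from it for an uninterrupted headache.

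**Conclusion.** The point holds as a flaw in how one secondary outcome is specified. The average cannot include everyone randomised unless every participant has an observed recurrence, and the article leaves open how an uninterrupted headache is counted.

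The stronger conclusion, that the comparison will be biased or will have the wrong sign, is not supported. Reversal needs particular assumed inputs. The recurrers-only mean typically reverses when ketamine participants who do recur do so sooner than placebo participants (5 against 7 days above); with 10 against 7 days it points the right way on average. The Cox reversal needs a sizeable arm difference in headaches that never stop, together with a decision to censor them. Every size quoted is illustrative, because the documents give no proportions.

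The change is worth making before unblinding, since the coding choice can affect the direction of the result. The primary analysis and the sample size are untouched.

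**What to change.** In Secondary outcomes, replace the average with: time from end of infusion to the first headache day, as defined under Primary clinical outcome, in all randomised participants. State that a participant with no headache-free day has an event on day 1, and that follow-up is censored at day 84 or at the last diary entry if earlier. Take this item out of the list assessed at baseline.

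In Statistical methods, name this as the event of the Cox model and report it with Kaplan-Meier curves by arm. The difference in restricted mean headache-free time to day 84, with a 95% confidence interval, is an optional addition that keeps a result in days.

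The cost is wording only. The daily diary already collects the data, and no visit, sample size or primary analysis changes.

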### Participant timeline

A 12-week trial during which the effect of high-dose ketamine infusion is compared to the saline infusion (placebo). The target of this trial is to demonstrate superiority. Outcomes will be assessed immediately after infusion and at 28 days, 56 days, and 84 days after infusion (Fig. 2).

**Fig. 2 Fig2:**
[figure not shown]
Schedule of enrollment, interventions, and assessments. -*t*1, 28 days before infusion; 0: day of infusion; *t*1, end of infusion; *t*2, at 7 days post-infusion; *t*3, at 28 days post-infusion; *t*4, at 56 days post-infusion; *t*5, at 84 days post-infusion

The screening for eligibility to participate in this trial and the informed consent occurs within 3 to 6 months before the intervention (Additional file 2: Appendix 2). The trial starts a month prior to the day of the infusion, as the patient will start tracking the number of headache days and the daily pain score 28 days prior to the infusion date. This baseline headache diary will be collected on the day of the infusion. On that same day, the participant will fill out the validated questionnaires (completing baseline assessment). Baseline data on sleep and physical activity will also be collected using actigraphy over 1 week prior to the trial infusion. Scheduled follow-up visits at 28, 56, and 84 days after the trial infusion will be performed in-person or virtually (video/phone) to assess trial-relevant outcomes.

### Sample size

A difference of 3 headache days (standard deviation (SD) of 3.8) in the frequency of headache days between the two groups in the 28 days after the trial infusion is considered as a minimum clinically important difference (MCID) [32] for this trial. A sample size of 25 participants in each group would have over 80% power to detect this difference between the 2 groups using a two-sided alpha of 0.05. Assuming a 10% drop-out rate 1 month after the infusions, 28 participants will be enrolled in each arm. This sample size is also robust to capture a key secondary outcome for this trial—a MCID of 1.0 (SD 1.3) in the mean 0–10 NRS score for average intensity of headaches in the first 28 days after the infusions (power of over 80% with a two-sided alpha 0.05) [14].

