## Assignment of interventions

### Randomization, sequence generation, and allocation concealment

Upon participant enrollment, patients will be randomized to one of two arms, with a 1:1 allocation and random permuted blocks of six. The randomization sequence will be computer generated by a member of the research team. The treatment allocation will be performed by an independent research coordinator not otherwise involved in the study, who will ensure allocation concealment by sequentially numbered, sealed opaque envelopes. This allocation sequence will be provided to the unblinded pharmacist

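### Stated power is slightly too high: 25 evaluable per group gives about 78% for headache days, and the NRS figure holds only if nobody drops out

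*Protocol article*

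**What the plan says.** All the figures are in the Sample size section of the protocol article. The target for the primary outcome is "A difference of 3 headache days (standard deviation (SD) of 3.8) in the frequency of headache days between the two groups" over the 28 days after infusion. The power claim is "A sample size of 25 participants in each group would have over 80% power to detect this difference between the 2 groups", with alpha set at 0.05, two-sided. Enrolment then follows: "Assuming a 10% drop-out rate 1 month after the infusions, 28 participants will be enrolled in each arm".

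The next sentence extends the claim to headache intensity: "This sample size is also robust to capture a key secondary outcome for this trial". The target there is "a MCID of 1.0 (SD 1.3) in the mean 0–10 NRS score for average intensity of headaches in the first 28 days", with "power of over 80% with a two-sided alpha 0.05". It does not say whether the sample size meant is the 25 evaluable or the 28 enrolled per arm.

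Allocation is "with a 1:1 allocation and random permuted blocks of six" (section on randomization, sequence generation and allocation concealment). The Statistical methods section names the independent t-test or the Wilcoxon rank sum test for continuous outcomes. It adds a baseline-adjusted ANCOVA for outcomes with a baseline from the preceding 28 days, and says that missing primary outcome data are not imputed. No baseline-to-outcome correlation is given.

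**The concern.** The section supplies every input needed to check its power figures, and the usual formulas return less than 80% for the primary outcome at the sample size it names. The NRS target is a slightly smaller standardized effect (0.769 against 0.789), so it cannot do better at the same number per group. It passes 80% only when the drop-out assumed one sentence earlier is set aside, although the NRS outcome covers the same 28 days.

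What is at stake is how a null result is read. The NRS comparison is singled out as a key secondary outcome with its own power claim. A reader would take the type II risk to be under 20%, whereas with 25 evaluable per group and an unadjusted t-test it is about 24% (100 − 76.0). For headache days it is about 22% (100 − 78.1).

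**Working it through.** **Inputs (Sample size section).** Headache days: difference 3, SD 3.8. NRS: difference 1.0, SD 1.3. Two-sided alpha 0.05, 1:1 allocation, 25 per group after 10% drop-out from 28.

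**Step 1, the plan's enrolment figure.** 25 / 0.90 = 27.8, rounded up to 28 per arm. In the other direction, 28 × 0.90 = 25.2, or about 25 evaluable. This part reproduces.

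**Step 2, the plan's n for the primary outcome.** Normal approximation: n = 2 × [(1.960 + 0.842) × SD / difference]². With 3.8 / 3 this is 25.2 per group, which rounds up to 26; the exact t-test needs 26.2, so 27. The stated 25 is within one or two participants per group of these figures.

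**Step 3, power at a given n.** Standardized effect d = difference / SD; noncentrality = d × √(n/2).

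- Normal approximation: power = Φ(noncentrality − 1.960).
- t-test: noncentral t with 2n − 2 degrees of freedom (critical value 2.011 at 48 df).

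Headache days: d = 3 / 3.8 = 0.789. At n = 25 the noncentrality is 0.789 × √12.5 = 2.791, so the normal approximation gives Φ(0.831) = 79.7% and the t-test gives 78.1%.

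NRS: d = 1.0 / 1.3 = 0.769. At n = 25 the noncentrality is 2.720, so the normal approximation gives Φ(0.760) = 77.6% and the t-test gives 76.0%.

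| Evaluable per group | Headache days, t-test | Headache days, normal | NRS, t-test | NRS, normal |
|---|---|---|---|---|
| 25 | 78.1% | 79.7% | 76.0% | 77.6% |
| 26 | 79.7% | 81.2% | 77.6% | 79.2% |
| 27 | 81.2% | 82.7% | 79.2% | 80.7% |
| 28 | 82.7% | 84.0% | 80.7% | 82.1% |

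The t-test first passes 80% at 27 per group for headache days and at 28 per group for the NRS.

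**Step 4, does baseline adjustment change this?** With an assumed correlation r between baseline and outcome, ANCOVA reduces the SD by the factor √(1 − r²). The t-test power at 25 per group (same degrees of freedom) becomes:

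| Assumed r | Headache days | NRS |
|---|---|---|
| 0 | 78.1% | 76.0% |
| 0.2 | 79.7% | 77.6% |
| 0.3 | 81.8% | 79.8% |
| 0.4 | 84.7% | 82.8% |
| 0.5 | 88.5% | 86.8% |

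Power reaches 80% at r of about 0.22 for headache days and about 0.31 for the NRS. These correlations are assumptions; the article gives none.

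**The case against.** Four points can be made for the plan.

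1. **The primary gap is small, and no formula is named.** By the normal approximation it is 0.3 points. The SD is printed to one decimal; if the unrounded value were 3.75, the normal approximation would give 80.7%. This has some force and is why the point is minor. But the rounding is a guess, the t-test at SD 3.75 still gives only 79.1%, and on the printed inputs neither formula exceeds 80%.

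2. **The NRS sentence may refer to 28 per arm.** The number immediately before it is the 28 enrolled, and at 28 the claim is true (80.7% by t-test). This stands as a reading of the grammar, so the NRS sentence cannot be called a plain arithmetic error. That reading does require that nobody is lost, over the same 28 days for which the preceding sentence assumes 10% loss.

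3. **The planned ANCOVA probably has more power.** Headache days and daily pain score both have a 28-day baseline diary, so the adjusted model applies to both, and modest correlations restore 80%. This limits the practical consequence. It does not rescue the printed figures, because the Sample size section neither refers to ANCOVA nor states a correlation.

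4. **A reader might infer that the trial is materially underpowered, or that enrolment must rise.** The documents do not support that. The primary deficit is one or two participants per group, small beside the uncertainty in any assumed SD, and the adjusted analysis already planned could more than cover it.

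**Conclusion.** The power statements are slightly overstated, and the point is minor. For the primary outcome, 25 evaluable per group gives about 78% by t-test (79.7% by normal approximation), a shortfall of 0.3 to 1.9 points against a claim of more than 80%. For the NRS, the claim holds at 28 evaluable per arm. At the 25 per group implied by the plan's own drop-out, power is about 76% (77.6% by normal approximation), 2.4 to 4.0 points short.

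These figures assume an unadjusted two-sided comparison of means with a common SD as printed, and 10% loss applying to the NRS as it does to headache days. No figure is offered for the rank sum alternative: its usual efficiency relative to the t-test is derived under normality, whereas the plan would turn to it when normality is in doubt.

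**What to change.** Change the power statements in the Sample size section and leave enrolment at 28 per arm. Either of these would do:

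- State that with 25 evaluable per group, power by unadjusted two-sided t-test is about 78% for headache days and about 76% for NRS intensity.
- Base the power on the baseline-adjusted ANCOVA already in the Statistical methods section and name the assumed baseline correlation. At 25 per group, 80% needs a correlation of at least about 0.22 for headache days and 0.31 for the NRS.

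In both cases, name the test and say whether each figure refers to evaluable or enrolled participants. The cost is one or two reworded sentences, with either a slightly less favourable stated power or one explicit assumption. Design, conduct and analysis stay as they are.
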